### Participant recruitment

The trial complies with the Declaration of Helsinki and Good Clinical Practice (GCP) guidelines. GCP compliance ensures that the rights, safety and well-being of research participants are protected and that research data are reliable. At sites, the local PI, research nurse or other member of the research team in conjunction with the clinical team will identify potential eligible participants, usually from current outpatient clinic lists or review of medical records. An anonymised log of all participants screened with reasons for exclusion will be kept at site. Information sheets for both adolescents and their parents/guardians will be provided to potentially eligible families. The relevant PIS will be given in person to families attending an outpatient clinic, or sent by post with a cover letter from the recruiting clinician. All families will be provided with contact details and informed that a member of the research team will contact them by telephone at least 24 hours after receipt of the information to discuss the study.

During this telephone call, the parent and adolescent will be given the opportunity to ask questions about the study and to confirm whether they are interested in participating. If interested, eligibility criteria will be checked with the parent to confirm suitability for the study and ascertain which parent will participate in the intervention and complete parent-rated outcomes. A summary of what to expect from the online screening and consent process will also be provided.

The process of explaining the study and determining eligibility of potential participants will be undertaken by an appropriately trained member of the research team as delegated by the PI, depending on local arrangements. All staff undertaking this process for this study must have completed GCP training provided by a responsible organisation (eg, University, NHS Trust) and must be authorised by the PI to explain the study and assess eligibility, on the site’s study delegation log.

### Online screening and consent

Informed consent and assent will be obtained via the study-specific website, developed and maintained by the UK Clinical Research Collaboration (UKCRC)-registered Peninsula Clinical Trials Unit (CTU) at Plymouth University.

#### Consent/assent

The consent process will depend on the age of the participants:Participants aged 16 to 18 years will provide online informed consent.Participants aged 12 to 15 years will provide online, informed assent. Those who have given assent and who reach the age of 16 years during the study, will be asked to provide online informed consent.Parents of all participants aged 12 to 15 years will provide online informed consent on behalf of their child (‘signature’ from one parent required).All participating parents will provide online informed consent for their own participation in the study.

#### Web-based consent process

The research nurse will enter on the study website brief details of those families who wish to participate in the study and who satisfy the initial inclusion/exclusion criteria. This will trigger an email to the adolescent, containing a link to the age-appropriate assent or consent form within the website, which the adolescent should complete.

Following completion of the adolescent assent/consent form, a separate email will be sent to the nominated parent participant containing a link to the parental consent form. Parents of adolescents aged 12 to 15 years will be asked to consent on behalf of their adolescent in addition to giving consent for their own participation. Two reminder emails will be sent from CTU followed by a ‘last chance’ email, all with reminders of the study link. If the family has not completed the consent process after 2 weeks, the local research team will be notified and will contact the family to ask if they still wish to participate in the study.

#### Face-to-face consent option

If the parent and/or adolescent has not completed the online consent process, CTU will inform the local research nurse who will telephone the family to offer the option of a clinic visit when the nurse can support the parent and/or adolescent to complete online consent/assent.

### Online BRIEF-2 parent-rating and allocation of study number

Following completion of the consent process, the parent will be prompted to complete the online Behaviour Rating Inventory of Executive Function, Second Edition (BRIEF-2)^34^ parent-rating questionnaire. If the parent does not wish to complete this immediately following the consent process, it will be possible to return to the website to complete it later. Two reminder emails will be sent from CTU followed by a ‘last chance’ email as above. Face-to face support to complete the BRIEF-2 will also be offered by the research nurse, as above. The parent must complete all elements of the BRIEF-2 before progressing to the baseline measures as this is the proposed primary outcome measure for a definitive trial.

The website will calculate the BRIEF-2 scores. The website will assign a unique four-digit study number to each participant and participants will be identified in all study-related documentation by this study number. An email to both the adolescent and the parent will then be sent, inviting them to follow a web link to complete the baseline measures, and informing them of their study number.

As part of the consent process, adolescents and parents will be reminded via the website that they are free to withdraw from the study at any time without giving a reason and without affecting further treatment.

### Baseline data collection (adolescent and parent self-completion)

On receiving the link to the baseline measures page of the study website, the adolescent and parent will complete their separate baseline questionnaires. The baseline measures should be completed within 2 weeks; if either the parent or adolescent have not undertaken these after 1 week, an email reminder to the parent (in all cases) and the adolescent (if adolescent measures not done) will be sent. In addition to the questionnaires, the parent will provide sociodemographic information, details of the adolescent’s past medical history and concurrent medication.

Participants will also be given the option of completing baseline measures with telephone support from a member of the research team. A £15 gift voucher will be sent to each family on completion of their baseline measures.

### Randomisation

Participants will be randomised via a web-based system created by the CTU in conjunction with the trial statistician, using minimisation by study site and type of brain injury (TBI/tumour/other). Participants will be randomly allocated in a 1:1 ratio to receive either TAU or TOPS-UK + TAU. The minimisation process will retain a stochastic element to retain allocation concealment. If any participant is found to be ineligible following randomisation, he/she will be excluded from analyses.

This study is not blinded. Following randomisation, the adolescent, parent, PI and research nurse will be notified by email of the adolescent’s treatment allocation, and this information will be held on the study site file. The parent and adolescent will also be advised when to expect further contact from the research team. In addition, the TOPS coach will be notified of all participants allocated to the intervention arm (TOPS-UK + TAU).

### Baseline data collection (research nurse)

The research nurse or another member of the research team at each site will record relevant injury characteristics data for each adolescent (including premorbid/developmental history) in the study-specific web-based case report form.

### Recording study participation in medical notes

The research nurse will make a record of study participation in the adolescent’s hospital notes according to local practice, stating that consent was obtained online and face-to-face support was given if appropriate. The research nurse will file a copy of the PIS in the hospital notes along with printed evidence from the study website of the informed consent process and who was involved. The nurse will also send a standard letter to the participant’s general practitioner recording study participation.

## Intervention

The study has two treatment arms, ‘TAU’ and ‘TAU + TOPS-UK’. Those allocated to the TAU + TOPS UK arm will work through the intervention programme taking 1 to 2 weeks per module. One coach will be trained to deliver the intervention to all of the participants in the intervention arm. The coach will coordinate the timing of the modules so that all families will have completed the intervention at 16 weeks. This will allow time for other commitments and holidays/breaks to be built into the schedule. The length of time taken to complete each module will be recorded to inform timing of follow-up in the main trial.

### Treatment as usual (control)

TAU will vary at each recruitment site because currently there is no evidence-based treatment for adolescents with pABI and their families. The type of TAU received will be recorded for each participant at baseline via a parent-rated measure of adolescent health and social care resource use (a modified version of the Client Service Receipt Inventory). There will be no opportunity for any TAU participants to receive the TOPS-UK intervention at any point during or after the study.

### Teen online problem-solving (intervention)

TOPS is an online intervention, which is provided by the Cincinnati Children’s Hospital website, via a link from the study website. For the purposes of this study, the US-based TOPS treatment content was edited to include British (English) spelling, narration and UK resource links, and modified to suit participants with pABI rather than traumatic brain injury only. All participants allocated to the TAU + TOPS-UK arm will be supported by a single TOPS-UK coach who will make weekly contact by video conference.

For those participants allocated to TAU + TOPS-UK, the TOPS-UK coach will contact the parent and/or adolescent by telephone, introduce themselves, discuss how to access the treatment modules on the website and how to log in for subsequent video call sessions. The coach will email these participants a ‘start-up’ pack describing how to access the online materials.

Ten subsequent sessions (table 2) consisting of self-guided didactic content regarding problem-solving skills, video clips modelling these skills and exercises to practise the skills, will then be completed every 7 to 10 days by the family and the adolescent with pABI. The online modules should take 30 min to complete, with the video call sessions taking 60 min. The parent will work together with the adolescent to complete the sessions. When the family has reviewed the materials for each session, the TOPS-UK coach will conduct a video call with the adolescent and parent who agreed to participate in the study. During this session they will review the online materials and practise the problem-solving skills using a problem identified by the family/adolescent. They will then plan the next session and agree a suitable time for the video call. Ideally, video calls will be held weekly, but this period can be increased as agreed through discussions between the coach and the family.

**Table 2 T2:** TOPS-UK sessions (complete 10 in total)

Core sessions (complete all five)	Getting started and staying positive
	Steps of problem-solving
	Getting organised
	Staying in control
	Taking care of you
Tailored sessions (choose four)	Dealing with fatigue
	Managing fear and worry
	Controlling your anger and improving communication
	Listening, talking and reading non-verbal cues
	Social behaviour and joining a group
	Working with the school
Core final session	Bringing it all together

TOPS-UK, Teen Online Problem-Solving, British version.

For all families allocated to TAU + TOPS-UK, the TOPS-UK coach will record details in the study database relating to intervention compliance for example, number and date of Skype sessions completed, length of each session, progress/engagement of adolescent and parent.

Completion of all 10 modules is expected to take each family 16 weeks in total. If the programme has not been completed after 16 weeks the intervention will be discontinued at that point. Study follow-up will proceed as if the programme had been completed.

### Sample size calculation

The study will aim to screen 20 potential participants at each site (n=100 in total), and aim to recruit a sample size of 25 participants from five sites. This should provide sufficient data to assess the feasibility and acceptability of the study. Although the sample size for the full RCT will be estimated based on the minimum clinically important difference for the BRIEF score^35^ (5-points), the SD for this patient population is currently unknown. A sample size of 25 is considered a realistic target and would be sufficient to address the feasibility aims (ie, acceptability of questionnaires etc), as well as aiming to provide at least 12 participants reporting quantitative baseline data to calculate the required SD.^36^

### Data management

The CTU data management team is responsible for data management. Each participant will be allocated a unique trial number on consenting to participate and will be identified in all study-related documentation by the trial number and initials. A record of names and addresses linked to participants’ trial numbers will be maintained by the research nurses at each site for administrative purposes and stored securely. This is an online study, with no requirement for data entry at CTU. Functions within the study website will remind participants to complete online measures, and flag up missing fields. However, participants will be able to progress through a questionnaire leaving data fields unfilled. The SQL Server database will be designed and maintained by the CTU data programming teams. Access by researchers will be password protected. In order to avoid problems with mislaid usernames and passwords, participants will access the web pages through links emailed to them by CTU. Once a web page has been completed by the participant it will be locked to prevent further data entry.

### Confidentiality

All data will be collected and managed in accordance with the Data Protection Act 1998. Each participant will be allocated a unique study number and will be identified in all study-related documentation by their study number and initials. All data will be entered on a password-protected SQL Server database and encrypted using a stored procedure. After all data cleaning has been performed and the database locked, anonymised data will be exported to the trial statistician.

### Data analysis plan

All randomised participants will be included in the analyses according to their randomised allocation, irrespective of adherence to treatment in the TOPS-UK arm or receipt of treatment in the TAU arm. No imputation of missing baseline or follow-up data will be performed. The study is not sufficiently powered to detect a significant treatment effect with regard to clinical or cost-effectiveness and thus a formal comparison will not be undertaken. The reported analyses will therefore be restricted to descriptive statistics on the outcome measures with appropriate point estimates (mean, median, percentage, etc), SD and 95% CIs for between group differences. For the questionnaire outcomes, approaches to missing individual items will be in accordance with the guidelines for missing item procedures for each questionnaire. Where no guidelines for individual missing items are available, the mean of the completed items will be used to replace missing items if 10% or fewer are missing. Statistical analyses will be performed following final data cleaning and locking of the dataset. No interim analyses are planned. All analyses will be performed using Stata V.14 and will be performed by a statistician using a data set with treatment allocation masked.

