**Trial registration number:**

ISRCTN10906069

Strengths and limitations of this studyThis is the first study to test an online problem-solving tool for adolescents who have survived a brain injury in the UK.The study explores the feasibility of recruitment strategies, data collection and economic evaluation to inform the design of a larger randomised controlled trial.The effect of the online intervention on executive functioning is not assessed.This study is conducted online, with minimal telephone support and no face-to-face contact.This feasibility study was conducted over a short time period thus limiting the opportunity for a long-term follow-up. The definitive trial would include a follow-up period of at least 6 months.

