#### Assessment of trial feasibility

The primary feasibility outcomes of this study include: (i) number of participants at each stage of the study, at each site, with stages including: identified as potentially eligible, approached, consented to study, completed screening and baseline, randomised (with at least five participants being recruited at each site), completed treatment and completed outcome assessments; (ii) any difficulties experienced at sites that may affect their ability to recruit in future will be identified and reviewed; (iii) evaluation of appropriateness of the trial and economic evaluation methods and procedures; (iv) assessment of participants’ willingness to be randomised to treatment allocation; (v) adherence to treatment assessed as number of sessions completed, a session will be recorded as complete if the participant has been through every page, reached the end and completed the coach web-linked session related to that material (with a target of participants completing at least five sessions) and (vi) attrition (with a target of at least 80% of participants completing follow-up assessments).

We will report the proportion of screened families who are found to be eligible, the proportion of eligible families who are recruited and randomised to their allocation and the proportion of randomised participants who provide outcome data at follow-up, with 95% CIs. Our sample size of 25 participants will allow us to estimate loss to follow-up (anticipated to be 20%) with a 95% CI of +/-13 percentage points. The further outcome is evaluation of the SD of the BRIEF-2 (parent) score for this patient population. This is the proposed primary outcome for the main trial and required for calculation of the sample size.^36^

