### Measurement of outcomes

This feasibility study aims to evaluate all aspects of the proposed fully powered RCT and cost-effectiveness analysis including recruitment and retention numbers, and completion of outcome measures proposed for the main trial. Outcomes will be assessed by questionnaires and interviews. Table 3 provides a summary of outcome measures for this feasibility trial.

**Table 3 T3:** Summary of outcome measures

Outcome group	Outcome measure	Objective	Evaluation time point(s)
Primary outcome (main trial)	Parent BRIEF-2	6	Baseline, 17 weeks post-randomisation
Secondary outcomes (main trial)	Adolescent: RCADS, SDQ, CBQ, BRIEF-2, CHU-9D Adult: RCADS, SDQ, EQ-5D-5L*, PHQ-9*, GAD-7*, CBQ, CSRI	1,10,11	Baseline, 17 weeks post-randomisation
Measures of adherence (intervention group)	Participation in weekly Skype sessions. Record of login to intervention website (frequency, duration, progression)	3,11	Data recorded by coach. Data captured automatically by database throughout 16 week intervention period.
Intervention feasibility and acceptability (intervention group)	Qualitative interviews with families Intervention acceptability questionnaires (adolescent and parent) Qualitative interview with coach	1–4, 6, 9	End of trial 17 weeks post-randomisation End of trial
Experience of TAU (TAU arm)	Qualitative interviews with families	15	End of trial
Study acceptability (both groups)	Study participation questionnaires (adolescent and parent) Qualitative interviews (adolescent and parent)	5	End of trial

*Measures relating to parental outcome.

BRIEF-2, Behaviour Rating Inventory of Executive Function, Second Edition; CBQ, Conflict Behaviour Questionnaire; CHU-9D, Child Health Utility 9D; CSRI, Client Service Receipt Inventory; EQ-5D-5L*, EuroQol 5 Dimensions 5 Levels Questionnaire; GAD-7*, Generalised Anxiety Disorder 7-item; PHQ-9*, Patient Health Questionnaire 9; RCADS, Revised Child Anxiety and Depression Scale; SDQ, Strengths and Difficulties Questionnaire; TAU, treatment as usual.

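### Between-group 95% CIs for the questionnaire outcomes read as raw differences, although a baseline score is collected, and the limitations list says the effect on executive functioning is not assessed

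*Protocol article*

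**What the plan says.** In the protocol article, the Data analysis plan says the study lacks power for a treatment effect, "thus a formal comparison will not be undertaken". It then limits the analysis to descriptive statistics: point estimates, "SD and 95% CIs for between group differences". It names no model and no covariate.

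Table 3 (Measurement of outcomes) gives the time points for the parent BRIEF-2 and for the secondary questionnaires as "Baseline, 17 weeks post-randomisation". The section on the online BRIEF-2 requires every element of the parent form to be completed before a family moves on. Under Randomisation, the minimisation factors are study site and type of brain injury, and baseline score is not among them.

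The list of strengths and limitations after the abstract states: "The effect of the online intervention on executive functioning is not assessed".

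**The concern.** Two things sit badly together.

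First, a raw difference in 17-week scores ignores a baseline measurement that the trial already collects. With about 20 completers the arms can differ noticeably at baseline by chance, and part of any such gap carries into the raw follow-up difference. The interval is also wider than it need be if baseline and follow-up scores are at least moderately correlated.

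Second, the BRIEF-2 measures everyday executive function. A randomised between-group difference on it, with a 95% CI, is an estimate of the intervention's effect on executive function, however imprecise. That does not agree with a flat statement that this effect is not assessed.

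What is at stake is the precision and face validity of the reported differences, and consistency between two parts of the article. The feasibility conclusions are not at stake.

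**Working it through.** **The plan's own figure.** The article gives no width for any between-group interval, so there is none to reproduce. Its one precision statement, to "estimate loss to follow-up (anticipated to be 20%) with a 95% CI of +/-13 percentage points", concerns a proportion and does not enter the comparison below; only the 20% is used. (It does not reproduce: 1.96 × √(0.2 × 0.8/25) = 15.7 points at 95%, while the 90% value is 13.2. That is a separate matter.)

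**Inputs from the article.**
- Sample size: "aim to recruit a sample size of 25 participants from five sites".
- Allocation: "Participants will be randomly allocated in a 1:1 ratio to receive either TAU or TOPS-UK + TAU".
- Completers: 25 × (1 − 0.20) = 20, or 10 per arm.
- Reference value: the 5-point minimum clinically important difference under Sample size calculation.

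**Assumptions.** The article says the SD is unknown in this population and gives no correlation. I take SD = 10 at both time points, and r from 0 to 0.8.

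**Raw difference.** Half-width = t(0.975, 18) × SD × √(1/10 + 1/10) = 2.101 × 10 × 0.447 = 9.4 points (0.94 SD).

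**Baseline-adjusted difference.** Half-width = t(0.975, 17) × SD × √(1 − r²) × √(1/10 + 1/10) × √(1 + 1/16). The last term, 1 + 1/(N − 4) with N = 20, is the average cost of estimating the covariate slope when the arms differ by chance at baseline. The constant part is 2.110 × 10 × 0.447 × 1.031 = 9.73.

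| r | Adjusted half-width (SD = 10) | Ratio to raw |
|---|---|---|
| 0 | 9.7 | 1.04 |
| 0.2 | 9.5 | 1.01 |
| 0.3 | 9.3 | 0.99 |
| 0.5 | 8.4 | 0.90 |
| 0.6 | 7.8 | 0.83 |
| 0.7 | 6.9 | 0.74 |
| 0.8 | 5.8 | 0.62 |

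The ratios do not depend on the assumed SD. With no loss (13 v 12) they are similar: 1.03 at r = 0, 0.89 at r = 0.5 and 0.73 at r = 0.7. Break-even lies between r = 0.2 and r = 0.3 in both cases.

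**Chance imbalance.** The SD of the baseline difference between arms is √(1/10 + 1/10) = 0.45 SD, or 4.5 points at SD = 10, close to the 5-point reference value. With equal SDs at the two time points, a fraction r of any imbalance carries into the raw follow-up difference. At r = 0.6 an imbalance of 4.5 points shifts it by 0.6 × 4.5 = 2.7 points. The adjusted estimate removes this shift.

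**Which outcomes have a baseline.** Tables 3 and 4 give a pre-randomisation score for the parent BRIEF-2 (listed under screening in Table 4) and for the secondary questionnaires. Adherence, attrition, intervention acceptability and study-participation feedback have none, and the primary feasibility outcomes are of this kind. Adjustment is therefore available only for the questionnaires proposed for the main trial.

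**The case against.** The strongest reply is that the article never says the differences are unadjusted. It is a condensed account, and covariates for a secondary descriptive summary are commonly left to the SAP. A reader might infer that the plan rules out baseline adjustment; it does not. What remains is that limiting the analysis to descriptive statistics is an affirmative restriction. A model-based difference fits awkwardly under it, so raw differences are the natural reading.

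A reader might also infer that the intervals are undeclared efficacy tests with a multiplicity problem, or that they will set the effect size for the definitive trial. The documents support neither. No test is planned, lack of power is stated, and Table 3 labels the measures as outcomes for the main trial. The definitive sample size rests on the minimum clinically important difference, with only the SD taken from this study.

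The gain rests on assumed values and changes no conclusion: at r = 0.5 to 0.7 with SD = 10, the adjusted half-width still exceeds 5 points. That is correct and limits the importance of the point.

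Adjustment also has a cost. Only the parent BRIEF-2 is complete at baseline by rule. Under Data management, fields in the other questionnaires can be left blank, and the Data analysis plan does not impute missing baseline data beyond its missing-item rules. An adjusted analysis of those measures could lose participants. This stands, and is a reason to keep the raw summaries as well.

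Finally, the limitations bullet can be read as shorthand for effectiveness not being tested. That is probably what was meant, but it is not what the sentence says.

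**Conclusion.** The point holds in a limited form. As written, the plan reads as raw between-group differences for questionnaires that also have a baseline score, where an adjusted estimate would usually be better and costs almost nothing. On the assumption of 10 completers per arm, the interval is 10% to 26% narrower for r between 0.5 and 0.7, with no gain below about 0.2 to 0.3. In points, assuming SD = 10, that is 9.4 falling to between 8.4 and 6.9. The correlation and the SD are assumptions.

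It would go too far to say that every outcome could be adjusted, since the feasibility outcomes have no baseline value, or that any feasibility target or the SD estimate is put at risk.

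The inconsistency over executive functioning is real but is one of wording: the descriptive, non-confirmatory status of the comparison is already stated in the Data analysis plan, and the limitations list should match it.

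**What to change.** 1. In the Data analysis plan (or the SAP), add: for questionnaire outcomes with a baseline score, above all the parent BRIEF-2, the between-group difference and its 95% CI come from a linear model with arm and the baseline value of the same measure, reported alongside the raw summaries by arm. Outcomes without a baseline stay as planned.
2. State the number of participants in each adjusted analysis, so that any loss through a missing baseline score is visible.
3. Reword the limitations bullet to say that effectiveness on executive functioning is not formally tested, in line with the Data analysis plan.

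The cost is one degree of freedom per model, a short addition to the analysis code, two or three sentences of text, and the possible loss of participants without a baseline score on measures other than the parent BRIEF-2. No new data are needed.
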